## Abstract

**Introduction:**

Secondary lymphoedema of the extremities is an important quality-of-life issue for patients who were treated for their malignancies. Indocyanine green (ICG) fluorescent lymphography may be helpful for assessing lymphoedema and for planning lymphaticovenular anastomosis (LVA). The objective of the present clinical trial is to confirm whether or not ICG fluorescent lymphography using the near-infrared monitoring camera is useful for assessing the indication for LVA, for the identification of the lymphatic vessels before the conduct of LVA, and for the confirmation of the patency of the anastomosis site during surgery.

**Methods and analysis:**

This trial is a phase III, multicentre, single-arm, open-label clinical trial to assess the efficacy and safety of ICG fluorescent lymphography when assessing and treating lymphoedema of patients with secondary lymphoedema who are under consideration for LVA. The primary endpoint is the identification rate of the lymphatic vessels at the incision site based on ICG fluorescent lymphograms obtained before surgery. The secondary endpoints are 1) the sensitivity and specificity of dermal back flow determined by ICG fluorescent lymphography as compared with ^99m^Tc lymphoscintigraphy—one of the standard diagnostic methods and 2) the usefulness of ICG fluorescent lymphography when confirming the patency of the anastomosis site after LVA.

**Ethics and dissemination:**

The protocol for the study was approved by the Institutional Review Board of each institution. The trial was filed for and registered at the Pharmaceuticals and Medical Devices Agency in Japan. The trial is currently on-going and is scheduled to end in June 2020.

**Trial registration number:**

jRCT2031190064; Pre-results.

## Introduction

1

Secondary lymphoedema of the extremities is an important quality-of-life issue for patients who were treated for their malignancies [1,2]. Lymphoedema is generally difficult to treat, and conservative treatment is the main treatment [3,4]. ^99m^Tc lymphoscintigraphy has been used for many years as one of the standard diagnostic methods of lymphoedema and is currently covered by the national health insurance of Japan [[5], [6], [7]]. However, lymphoscintigraphy has the following disadvantages: high costs, large-sized equipment for examination, low resolution, and radiation exposure.

Since 2007, fluorescent lymphography with indocyanine green (ICG) for assessing lymphoedema has been introduced [[8], [9], [10], [11], [12], [13], [14], [15], [16], [17], [18], [19], [20], [21], [22], [23], [24], [25]]. ICG fluorescent lymphography has been reported as a potentially useful assessment method to depict the lymphatic vessels in real time and to assess their function at low cost. ICG fluorescent lymphography allows the monitoring of time-course changes in the morphology and function of the lymphatic vessels and can be conducted anywhere including the examination and operation rooms [[8], [9], [10], [11], [12]]. A retrospective study showed a significant correlation in lymphoedema severity between ICG fluorescent lymphography and lymphoscintigraphy [10]. The usefulness of lymphaticovenular anastomosis (LVA) is well recognized among lymphatic microsurgeons, and ICG fluorescent lymphography has evolved as a reliable assessment method of extremity lymphoedema. In recent years, the usefulness of LVA that improves lymphatic flow has been reported [[26], [27], [28]].

ICG fluorescent lymphography using the near-infrared monitoring camera utilizes the following properties: 1) ICG is excited by irradiating the near-infrared ray of 760 nm in wavelength, and fluorescence of 830 nm in wavelength is thus generated; and 2) ICG, which was injected subcutaneously, is mostly bound to albumin and is then incorporated and delivered into the lymphatic vessels [8]. The use of the near-infrared monitoring camera permits the demonstration of the current direction of ICG in the lymphatic vessels and of the regurgitation of the lymphatic valves, thus allowing the depiction of dermal back flow—a finding characteristic of lymphoedema. Furthermore, the camera quite excels in allowing the real-time confirmation of lymph dynamic. Some studies reported a significant correlation between pathological stages determined by ^99m^Tc lymphoscintigraphy and ICG fluorescent lymphography; however, the ICG findings appropriate for LVA have not been standardized [[10], [11], [12]].

ICG fluorescent lymphography is expected to help the appropriate selection of patients with lymphoedema who are indicated for LVA, to serve for the identification of the lymphatic vessels before and during surgery and for the confirmation of the patency of the anastomosis site, and to greatly contribute to an improvement in the therapeutic outcomes of patients with lymphoedema; however, all of them need to be investigated in a prospective clinical study.

The objective of the present clinical trial is to confirm whether or not ICG fluorescent lymphography using the near-infrared monitoring camera is useful for specifying patients to whom LVA is indicated, for lymphatic vessel identification before the conduct of LVA, and for the confirmation of anastomosis site patency during surgery.

## Methods

2

### Trial design

2.1

The present clinical trial is a multicentre, collaborative, confirmatory, single-arm, open-label study. All patients with secondary lymphoedema in the lower or upper extremities, who are under consideration for LVA at the participating institutions, will receive written and oral information about the HArmonised Medical Assessment of lyMphoedemA based on The diagnoStic Usefulness of fluorescent lymphography with IndoCyanine Green (HAMAMATSU-ICG) study.

In this study, the primary endpoint can be verified only in patients with radiographic evidence of lymphostasis and the presence of the anastomosable lymphatic vessels, who are candidates for LVA. Therefore, patients who meet the inclusion criteria and do not fall under any of the exclusion criteria for this study should receive investigational drugs after registration to assess the presence of lymphedema and anastomosable lymphatics. Two types of registration are established in this study: the primary registration—the registration of patients to be conducted at the onset of the assessment phase; and the secondary registration—the registration of patients to be conducted at the onset of the treatment phase. After the primary registration, patients should be evaluated in the assessment phase, and those who meet the inclusion criteria and do not fall under any of the exclusion criteria for the secondary registration should be evaluated in the treatment phase. Patients who meet the eligibility criteria for primary registration should undergo ICG fluorescent lymphography and ^99m^Tc lymphoscintigraphy. LVA should not be conducted for ineligible patients among them, and the present study should be discontinued for the former. Patients who meet the eligibility criteria for secondary registration will undergo preoperative and intraoperative ICG fluorescent lymphography. The trial outline is schematised in Fig. 1.

**Fig. 1 fig1:**
[figure not shown]
Diagram of the study outline. ICG, indocyanine green; LVA, lymphaticovenular anastomosis. (For interpretation of the references to colour in this figure legend, the reader is referred to the Web version of this article.)

### Eligibility criteria

2.2

A patient, who meets all of the following conditions, should be subject to the primary registration: 1) who was diagnosed with secondary lymphoedema of the extremities based on clinical symptoms; 2) who was diagnosed with stage I to II lymphoedema from their clinical symptoms as defined by the International Society of Lymphology, which was categorized from stage 0-III; 3) who was 20 years of age or older at the time of informed consent acquisition; and 4) who gave his/her free will-based written informed consent after receiving a sufficient explanation prior to enrollment in the present clinical trial and based on a sufficient understating about the present clinical trial.

A patient, who falls under any of the following conditions, should not be subject to the primary registration: 1) who has primary lymphoedema; 2) who has allergy against iodine; 3) who has shown shock caused by ICG administration in the past; 4) who has shown symptoms of allergy caused by ^99m^Tc administration in the past; 5) who has allergy against xylocaine; 6) who is lean (body mass index [BMI]: <18 kg/m^2^) or obese (BMI: > 30 kg/m^2^); 7) who is a woman being pregnant, being breast-feeding, or willing to become pregnant during the study period; 8) who was otherwise considered inappropriate for enrollment in the clinical trial by the investigator; or 9) who has lymphoedema in both the upper and lower extremities, thus not allowing limitation to either the upper or lower extremities.

A patient, who meets all of the following conditions, should be subject to the secondary registration: 1) in whom the site of linear pattern was confirmed by ICG fluorescent lymphography after the primary registration; and 2) who was diagnosed with lymphoedema by ^99m^Tc lymphoscintigraphy after the primary registration.

A patient, whose ICG fluorescent lymphograms fall under any of the following conditions, should not be subject to the secondary registration: (1) in whom the linear pattern cannot be confirmed because of presenting only the “area of dermal back flow pattern that is indicative of the reversed current of the collecting lymphatic vessels into the skin” and the “area where a fluorescent lymphogram is not found at all,” which led to the judgment that the lymphatic vessels are difficult to identify; (2) who was otherwise judged to be inappropriate as a subject to the present trial; (3) who has had symptoms of allergy caused by the subcutaneous injection of ICG; or (4) who was diagnosed to have oedema due to causes other than lymphoedema because of presenting normal lymphoscintigraphic findings.

### Recruitment

2.3

This trial was filed for and registered at the Pharmaceuticals and Medical Devices Agency (PMDA) in June 2019. Recruitment started in July 2019 and was completed in March 2020 because 55 patients were registered, which exceeded the target number of 50 patients with lymphoedema for the secondary registration. This study is being conducted at 4 university hospitals in Japan.

### Sample size calculation

2.4

None of previous articles refer to the identification rates of the lymphatic vessels in patients with lymphoedema when conducting and not conducting ICG fluorescent lymphography. A multicentre clinical trial of ICG on sentinel lymph node biopsy in patients with breast cancer was designed to indicate its efficacy at a lymph vessel identification rate of 90%. Consequently, the lymph vessel identification rate was 99.6% [26].

ICG should be considered useful when the positivity rate is 90%. The target number of patients for the present clinical trial was calculated to be 118, when assuming a threshold of 80% and an expected value of 90% (90% power, 5% two-sided significance level).

Usually, LVA is conducted at 5 or more sites of an extremity. To avoid verifying the accuracy of lymphatic vessel identification several times for the same lymphatic vessels in a certain area, the extremity is divided into 4 areas and the number of examinations in each area is limited. Verification is expected to occur in 3 or more sites on average, and any upper limit is not established for the points to verify the accuracy of lymph node identification as long as the protocol is followed. The target number of patients with lymphoedema for the secondary registration, which is good enough to examine 150 sites, should be set at 50.

### Interventions

2.5

ICG fluorescent lymphography should be conducted to achieve the following objectives according to the schedule for 3 active study visits:

#### ICG fluorescent lymphography to assess lymphoedema in the ICG administration phase [assessment phase] after the primary registration

2.5.1

1)Local anaesthesia with 0.5% xylocaine should be conducted beforehand at the planned site for ICG subcutaneous injection. The 2.5 mg/mL ICG solution (Diagnogreen®, 25 mg: Daiichi Sankyo Co., Ltd, Japan) should be injected subcutaneously to the right and left, upper or lower extremities. The target extremities should include 5 sites per extremity (upper extremities: the second interdigit, the fourth interdigit, the distal three-fourths point on the straight line that connects the distal end of the radial styloid process and the head of the first metacarpal bone, the distal end of the ulnar styloid process, and the distal forearm at the level of the tendon for long palmar muscle; and lower extremities: the first interdigit, the fourth interdigit, below the medial malleolus, below the lateral malleolus, and the midpoint on the straight line that connects the head of the fifth metatarsal bone and the lateral malleolus (Fig. 2) [27]. The 2.5 mg/mL ICG solution, 0.2 mL per site, should be injected subcutaneously.

**Fig. 2 fig2:**
[figure not shown]
Five sites for ICG injection: (A) hand and (B) foot ICG, indocyanine green. (For interpretation of the references to colour in this figure legend, the reader is referred to the Web version of this article.)2)With the patient on bed who is in the supine position and at rest and under indoor illumination that is reduced immediately after subcutaneous injection, the near-infrared monitoring camera (Pde-neo®, Hamamatsu Photonics K·K., Japan) will be used to monitor and record the imaging findings on the extremity surface. Regarding the lower extremities as well, recording should be conducted with the patient in the prone position. ICG, which is retained in the hypodermis, should be drained manually to quickly confirm the course of the collecting lymphatic vessels. ICG fluorescent lymphograms can be categorized to the following regions: A) the region of linear pattern where the pre-collecting lymphatic vessels or collecting lymphatic vessels are depicted in a linear pattern; B) the region of dermal back flow pattern where the reversed current of lymph of the collecting lymphatic vessels into the skin is obvious; and C) the region where any fluorescent image cannot be seen at all (Fig. 3). The image should be obtained immediately after injection. In patients in whom findings in the entire extremities cannot be obtained immediately after injection due to the slow movement of ICG, imaging should be conducted again at a later time without reinjection, and the time from injection to reimaging is recorded. However, the check of the findings should be completed not later than 3 h after injection.

**Fig. 3 fig3:**
[figure not shown]
ICG fluorescent lymphograms can be categorized to the region of linear pattern, the region of dermal back flow pattern, and the region where any fluorescent image cannot be seen at all. (A): Linear pattern, (B): Dermal back flow pattern.ICG, indocyanine green. (For interpretation of the references to colour in this figure legend, the reader is referred to the Web version of this article.)3)^99m^Tc lymphoscintigraphy using the injection solution of a radiopharmaceutical agent, standard human serum albumin diethylenetriamine pentaacetic acid technetium (^99m^Tc) (Poolscinti® Injectable), should be conducted in all patients who were included in the primary registration within 8 weeks after ICG fluorescent lymphography in order to determine the sensitivity and specificity of lymphoedema diagnosis by ICG fluorescent lymphography when considering ^99m^Tc lymphoscintigraphy as one of the standard diagnostic methods. ^99m^Tc lymphoscintigraphy should be conducted at 120 min after radioisotope administration.

#### Fluorescent ICG lymphography before surgery to identify the lymphatic vessels in the investigational drug administration phase [treatment phase] after the secondary registration

2.5.2

1)Local anaesthesia with 0.5% xylocaine should be conducted beforehand at the planned sites for ICG subcutaneous injection. ICG should be injected subcutaneously to the extremity where LVA is intended. The target extremities should include 5 sites per extremity (Fig. 2). The 2.5 mg/mL ICG solution, 0.2 mL per site, should be injected subcutaneously.2)With the patient on bed who is in the supine position after subcutaneous injection, a red pen should be used to mark the skin on the confirmed fluorescent lymphograms of linear pattern.3)The incision site for LVA should be determined at the site where the linear pattern was found. The depicting ability of ICG is estimated to differ depending on the thickness of the skin and subcutaneous adipose tissue. Therefore, 4 areas should be established in distal-to-proximal order in both the upper and lower extremities (Fig. 4). The maximal number of skin incision sites for lymphatic vessel dissection should be 2 to avoid the repeated identification of the same lymphatic vessels in the same region. Furthermore, the skin incision site for research in the same area should be one for the continuing linear pattern. This arrangement is to avoid the mutual influences among multiple sites of anastomosis and to ensure their independency. The length of skin incision should be determined in response to the thickness of subcutaneous fat, ranging from 0.5 cm to 2.0 cm. Surgery should be conducted under general or local anaesthesia. The camera for visible light should be used to photograph and record the findings as to whether the anastomosable collecting lymphatic vessels are successfully identified in reality on the line of skin incision that was set before surgery (Fig. 5).

**Fig. 4 fig4:**
[figure not shown]
Both the upper and lower extremities were divided into the following 4 areas—lower extremities: 3 borders established at 6 cm proximal from the centre of the medial malleolus, 4 cm distal from the popliteal fossa, and 4 cm proximal from the popliteal fossa; and upper extremities—3 borders established at 6 cm proximal from the ulnar styloid process, 4 cm distal from the cubital fossa, and 4 cm proximal from the cubital fossa.

**Fig. 5 fig5:**
[figure not shown]
(A): ICG fluorescent lymphogram of the forearm and (B): an image of the same region under visible light. The skin incision site was determined preoperatively on the linear pattern of an ICG fluorescent lymphogram. (C): A photograph under visible light should be used to confirm whether the anastomosable collecting lymphatic vessels are successfully identified in reality on the line of skin incision.

#### ICG fluorescent lymphography during surgery to check the patency of the anastomosis site after LVA in the investigational drug administration phase [treatment phase]

2.5.3

LVA should be conducted in the case that the veins appropriate for LVA were confirmed in the periphery of the identified lymphatic vessels. After anastomosis, the surgeon should judge (a) patency, (b) nonpatency, or (c) unclearness according to the conventional methods: (1) visual confirmation of the movement of lymph or blood at the anastomosis site; and (2) examination of patency—a method by which 2 tweezers are used to transiently generate a fluid-free condition between the tweezers by stemming the venous flow with them, followed by the confirmation of fluid movement at the anastomosis site after lifting only the tweezer that was placed on the peripheral side. After confirmation according to the conventional methods, the surgeon should subcutaneously inject 0.2 mL of ICG 2.5 mg/mL solution into the site distal from each anastomosis site and should judge (a) patency, (b) nonpatency, or (c) unclearness based on the findings of ICG fluorescent lymphography. The schedule for the study visits and data collection is summarized in Table 1.

**Table 1 tbl1:** Schedules for the conduct of the clinical trial. The schedules to conduct monitoring, testing, and assessment are shown in the table below. The investigator or subinvestigator should conduct monitoring, testing, and others in accordance with the schedule.

	Consent acquisition	Screening phase		Investigational drug administration phase [assessment phase]		Investigational drug administration phase [treatment phase]		At the time of comple-tion Day 7	At the time of discon-tinuation
		Screening test		ICG (investigational drug)	Scintigraphy	Testing and treatment phase (hospitalization and control)			
	Visit Day 1 Weeks −26 to −9			Visit Day 2 Weeks −17 to −9	Visit Day 3 Weeks −17 to −1^a^	Day of imaging before surgery Day −1	Day of surgery Day 1		
Allowable range	–			–	*****	+1	–	±1	+3
Written informed consent	●								
Primary registration			●						
Secondary registration					●				
History taking of the subject's background			●						
History taking of the primary disease, anamnesis, and complications			●						
Measurement of vital signs			●	●	●	●	●	●	●
Blood sampling (hematology, blood chemistry)^b^			●					●	●
Physical examination (measurement of the circumference of the upper or lower extremities of both sides)			●					●	●
Urinalysis			●						
Pregnancy test^c^			●						
Diagnostic ICG fluorescent lymphangiography				●					
^99m^Tc lymphoscintigraphy (the extremities of both sides)					●				
Photography of appearance			●						
Classification of International Society of Lymphology stages			●						
ICG fluorescent lymphangiography before surgery						●			
ICG fluorescent lymphangiography during surgery (examination of patency)							●		
Monitoring of adverse events^d^				●					●
Check of defects				●					●
Check of concurrent drugs and concurrent therapies			●						●

a Visit Day 3 (day of scintigraphy) should be the same day as visit Day 2 (day of ICG lymphangiography) or within 8 weeks.

b Hematology: WBC, RBC, Hb, Hct, Plt, differential leukocyte counts (neutrophils, lymphocytes, monocytes, basophils, and eosinophils), and prothrombin time Blood chemistry: AST, ALT, ALP, γ-GTP, LDH, T-Bil, D-Bil, TP, Alb, Glu, T-Cho, HDL, TG, UA, BUN, Cre, Na, K, Cl, ChE, and HbA1c.

c Not required for patients about whom the potential of pregnancy can be denied (e.g., women who underwent hysterectomy and menopausal women).

d All of adverse events, which occurred from the first subcutaneous injection of ICG in the investigational drug administration phase [assessment phase] to the completion of the trial period (Day 7).

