### Primary endpoint

3.1

The primary endpoint of this study is to calculate the identification rate of the lymphatic vessels at the incision site only in patients who are indicated for LVA based on the following requisites: the radiographic evidence of lymphatic stasis; and the presence of the anastomosable lymphatic vessels. Therefore, the investigational drug should be administered in the primary and secondary registration. Patients who meet the eligibility criteria for the primary registration will be assessed in the assessment phase and will undergo ICG fluorescent lymphography and lymphoscintigraphy. LVA will not be conducted for those whom the procedure is not indicated, and the study will be discontinued. Furthermore, patients who meet the eligibility criteria for the secondary registration will be assessed in the treatment phase and will undergo preoperative and intraoperative ICG fluorescent lymphography. The third-party expert panel independent from the present clinical trial should make the final judgment based on the triad of fluorescent lymphograms before surgery, light images before surgery, and the photographs of the lymphatic vessels that were taken after skin incision during surgery.

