This study has several limitations. First, this study is intended to examine patients who are indicated for the surgical treatment of secondary lymphoedema and does not aim to examine patients about whom the cause of lymphoedema was determined (e.g., patients with venous disease or suspected primary lymphoedema). Since the primary endpoint of this study is to calculate the lymphatic vessel identification rate in LVA, we will enroll patients who are scheduled to undergo LVA based on their clinical findings. Patients, in whom venous disease is the primary cause of lymphoedema, should be excluded from this study because LVA is not indicated for them. In addition, the usefulness of LVA for patients with primary lymphoedema has not been proved. We will intend to examine the usefulness of ICG fluorescent lymphography in differentiating lymphoedema caused by lymphatic and venous diseases once the results from this study are obtained. Second, the present study is designed neither to provide the long-term outcomes of LVA, nor to verify the safety of LVA. Any conclusive and globally acceptable views are still not obtained with respect to its superiority to therapeutic modalities including conservative therapy for lymphoedema and to its applicability, constituting a great clinical challenge to be addressed [[33], [34], [35]]. The present clinical study is intended to preliminarily verify the usefulness of ICG fluorescent lymphography in assessing secondary lymphoedema and to determine the accuracy of depicting the collecting lymphatics and dermal back flow—an indication for LVA. We expect the present study be a foundation for future clinical studies to assess the surgical treatment of secondary lymphoedema. Third, patients with subclinical lymphoedema are excluded from the present study although the prophylactic treatment of and surgical intervention for them have been reported [15,36]. Since the severity of lymphoedema—based on which LVA is indicated for patients with subclinical lymphoedema—remains to be determined, which causes a dispute. Therefore, this study aims to examine patients with lymphoedema who show dermal back flow—a common indication for surgery. Fourth, 2 sessions of ICG fluorescent lymphography, one each in the assessment and treatments phases, and should be separated by an interval of at least 8 weeks to avoid the effects of residual ICG. On the other hand, the interval between ICG fluorescent lymphography and ^99m^Tc lymphoscintigraphy in the assessment phase should be shorted to the extent possible. We consider that the ≤ 8-week-interval of ICG fluorescent lymphography and ^99m^Tc lymphography in the assessment phase is acceptable because the present study enrolls patients with chronic lymphoedema of the extremities who are undergoing conservative therapy. In the case that significant changes (e.g., the disappearance of the linear pattern of lymphoedema on ICG fluorescent lymphograms in the treatment phase) occurred, we will analyze the relevant changes in a short interval.

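### Table 1 schedules one pregnancy test, at screening, and no repeat, so the test is at least about 8 weeks old at the Day −1 ICG session and at surgery

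*Protocol article*

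**What the plan says.** The row "Pregnancy test^c" in Table 1 carries one mark, in the screening sub-column shared with primary registration. Nothing is marked at the first ICG session, scintigraphy, Day −1, the day of surgery, Day 7 or discontinuation. Footnote c gives an exemption, "Not required for patients about whom the potential of pregnancy can be denied (e.g., women who underwent hysterectomy and menopausal women", and no validity period or repeat for the other women. The table legend makes the schedule an instruction to sites: "The investigator or subinvestigator should conduct monitoring, testing, and others in accordance with the schedule".

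These places fix the timing:

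- Section 2.1 puts primary registration at the start of the assessment phase and gives the drug only after registration.
- Table 1 sets Visit Day 1 at weeks −26 to −9 and the first ICG session at "Visit Day 2 Weeks −17 to −9".
- Under footnote a, scintigraphy "should be the same day as visit Day 2 (day of ICG lymphangiography) or within 8 weeks". Section 2.5.1 requires it "in all patients who were included in the primary registration within 8 weeks after ICG fluorescent lymphography".
- The Discussion (section 6) says the two ICG sessions "should be separated by an interval of at least 8 weeks to avoid the effects of residual ICG".

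On eligibility, section 2.2 bars women who are pregnant, breast-feeding or intending to conceive from primary registration. None of the four secondary-registration exclusions names pregnancy, though one is a general clause for unsuitable subjects.

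**The concern.** The plan treats pregnancy as a reason not to enter a woman, and it schedules a test to enforce that. The enforcement happens once, before the first ICG session. Several exposures follow: the 99mTc tracer, a second ICG session on Day −1, further ICG at each anastomosis, and an operation with general or local anaesthetic. A site that follows Table 1 to the letter carries out the last three on a result that is about two months old or older. The secondary registration would be the natural point to look again, but the plan asks for no test there.

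What is at stake is an avoidable exposure in a woman with an unintended and unnoticed pregnancy. The documents give no fetal-risk figure for ICG or for the tracer, so the harm cannot be sized from them.

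**Working it through.** The plan gives no figure for the age of the test, so there is none to reproduce. The age follows from the visit windows and the gap rule.

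**Most favourable reading: test on the day of the first ICG session.** Pregnancy bars primary registration, and dosing comes after registration, so the test can fall no later than this day.

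- Age at the Day −1 ICG session = gap between the two ICG sessions ≥ 8 weeks = 56 days.
- Cross-check against the windows: week −9 gives 9 × 7 − 1 = 62 days, or 8 × 7 − 1 = 55 days if the last day of that week is used (about 7.9 to 8.9 weeks). Where the window gives 55 days, the 8-week gap rule governs.
- Upper end, first ICG session in week −17: 17 × 7 − 1 = 118 days, about 17 weeks.
- Age at surgery: a day or two more.
- Age at scintigraphy: 0 (same day) to 8 weeks.

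**Literal reading of the Visit Day 1 window: test as early as week −26.**

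- Age at the Day −1 ICG session: 26 × 7 − 1 = 181 days, about 26 weeks. This is the indirect cap.
- Age at the first ICG session in week −9: up to 26 − 9 = 17 weeks.
- Age at scintigraphy in week −1, 8 weeks after that session: up to 17 + 8 = 25 weeks.

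**Exposure after the only test** (sections 2.5.2 and 2.5.3).

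- Day −1: 5 sites × 0.2 mL × 2.5 mg/mL = 2.5 mg ICG.
- Surgery: 0.2 mL × 2.5 mg/mL = 0.5 mg ICG per anastomosis.

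**Who is affected.** Only women not exempt under footnote c. Those found unsuitable for lymphaticovenular anastomosis (LVA) leave before the treatment phase (section 3.1: "LVA will not be conducted for those whom the procedure is not indicated, and the study will be discontinued"), so for them the issue arises at scintigraphy at most. The article does not say how many patients are non-exempt women.

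**The case against.** The strongest reply is that this is a condensed article. Rules on re-testing, contraception and pre-operative checks often sit in the full protocol, and a hospital may test before an operation anyway. Table 1 marks no blood sampling between screening and Day 7, so it may well leave out routine pre-operative work-up. That stands as a reason for caution about what sites actually do. It does not supply a repeat test: the article prints the schedule row by row and tells investigators to follow it, so a single mark is a stated frequency.

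A second reply is that blank cells in this table are weak evidence, because the adverse-event row has only two marks while footnote d requires monitoring throughout. Those two marks can be read as the ends of a span. The pregnancy row has one mark and no second end, and the vital-signs row shows that the table repeats its marks where a procedure is repeated.

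Third, the plan already reduces the risk. Women who intend to conceive are excluded, and the general clause at secondary registration can remove a known pregnancy. Both are true, but neither detects an unintended one.

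Fourth, on scintigraphy, the Discussion asks for the interval from ICG to be kept as short as possible, and footnote a allows the same day. This stands and weakens that part of the point: 8 weeks is what the plan permits there, not what it aims for.

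A reader might also infer that the test has no age limit at all. The Visit Day 1 window does limit it, at about 26 weeks before surgery, although that is a visit window and not a validity rule.

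**Conclusion.** The point holds as a minor safety matter. For every non-exempt woman in the treatment phase, the only scheduled pregnancy test is at least about 8 weeks old at the Day −1 ICG session and at surgery. It can be about 17 weeks old if done with the first ICG session, and about 26 weeks old if done at the earliest screening date. At scintigraphy it may be 8 weeks old or more, subject to the request for a short interval.

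The lower bound rests on two things: the 8-week gap between ICG sessions, and the test falling no later than the first ICG session. It also assumes that the full protocol adds no repeat that the article omits.

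Stronger readings are not supported. The plan does not contradict itself or allow a woman known to be pregnant to enter: pregnancy is excluded at primary registration. The number of women or pregnancies affected cannot be derived from the article and is probably small. Nothing here bears on the primary endpoint, the analysis or the sample size.

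**What to change.** For women not exempt under footnote c, add to Table 1:

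1. a urine pregnancy test at Day −1, before the pre-operative ICG injection;
2. a urine pregnancy test before scintigraphy, when that is not done on the same day as the screening test or shortly after it.

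Name pregnancy among the secondary-registration exclusions in section 2.2. The Day −1 test comes after secondary registration, so also state that a positive result stops the woman before the Day −1 ICG session and surgery. If the full protocol already requires a repeat, show it in Table 1.

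The cost is two marks in one row, a line or two of eligibility and stopping text, and one or two urine tests per non-exempt woman at visits that already exist. Recruitment closed in March 2020 with 55 registered, and the trial was due to end in June 2020, so the change reaches only women still awaiting these visits and any later use of the schedule. If the 55 are secondary registrations, they had already had scintigraphy, because a scintigraphic diagnosis is required for that step. The scintigraphy test would then matter only for later use.
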